### Power and sample size calculation

An F-test over three groups with a medium effect-size of treatment compared to waiting list, alpha .05 and power .80 needs 159 participants. Attrition is estimated conservatively to be high at 33%. The needed number of participants is 240. We will use 3 x 80 participants.

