The auditory Random Interval Repetition (RIR) task is a computerized reaction time task, that is studied as a possible predictor and moderator of treatment outcome. During this task participants wear headphones that present repetitive beeps of 200 Hz, each lasting for 50 ms. The inter-stimulus-interval (ISI) on this computerized RIR task is either 850 or 1450 ms. Participants are instructed to respond as fast as possible by pressing a bar, every time they hear a beep, and the reaction time (RT) is the dependent variable. The RIR task is carried out under two conditions of three minutes each: 1) while making a distracting task, in this case eye movements, elicited by the index-finger of the research assistant, moving horizontally at 30 cm from the eyes at a pace of two seconds per cycle, and 2) without a distracting task. The order of the conditions is counterbalanced to control for carry over effects. The degree to which eye movements tax the central executive component of the working memory is operationalized as the slowing down of RTs and reduced accuracy (more errors and non-responses) during the distracting task compared with the no-distracting task condition. The task is constructed and performances measured with E-Prime 1.2 software.

To have a RT task carried out while the subject is being distracted simultaneously, is a valid way to assess the presence and severity of cognitive taxing [114]. RTs to auditory cues presented at an RIR task, provide a valid and highly sensitive measure of taxation of the central executive component of the working memory [115]. Laboratory experiments with undergraduates have shown that 1) making eye movements during a stimulus discrimination task slows down RTs and raises the number of errors made [116] and 2) more taxing of the working memory results in higher RTs, more errors and more non-responses [117]. In a pilot study with 12 patients with a psychotic disorder we found the same patterns in the performance on the RIR task with three conditions: no eye movements, eye movements at one second per cycle and eye movements at two seconds per cycle (publication in preparation). In T.TIP two seconds per cycle will be used.

Several measures of treatment credibility, burden, harm expectancy and harm experience are administered to both therapists and participants.

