### Analyses

The primary outcome on the PTSD measures will be analyzed using Linear Mixed Models (LMM) with the baseline value as a covariate. LMM will also be used with the secondary outcome measures. Sensitivity and specificity of the screener will be calculated with Receiver Operating Characteristic curves. The predictors will be assessed with (logistic) regression analysis. The moderator and mediator analyses will be calculated with 5,000 bootstraps [124]. The association between working memory and the outcome of therapy is performed by analysis of covariance (ANCOVA’s) and multiple regression analysis. The ESM data will be analyzed by multilevel linear regression modeling using STATA. In case of an effective treatment a cost-effectiveness analysis will be performed. The incremental cost-effectiveness ratios (ICERs) are considered to be a single-point estimate of an underlying continuum. Acceptability curves are produced with bootstrap simulations and confidence intervals. The outcome will be costs in Euro’s per QALY and the costs in Euro’s per day without PTSD gained. If no intervention is effective, which is not expected, a cost-minimization calculation will be done.

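### Counterbalancing the block order of the working-memory task protects the group mean but not the individual score used as predictor and moderator, so any order effect weakens those analyses unless order is used

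*Protocol article*

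**What the plan says.** The section on moderators, mediators and predictors introduces the RIR as a reaction-time task "that is studied as a possible predictor and moderator of treatment outcome". On its layout it says: "The RIR task is carried out under two conditions of three minutes each", one block with eye movements and one without. The score is a contrast between those blocks: "The degree to which eye movements tax the central executive component of the working memory is operationalized as the slowing down of RTs", together with lower accuracy, relative to the block without distraction. On sequence the article says "The order of the conditions is counterbalanced to control for carry over effects". Table 4 places the RIR at T0 only, so there is no second administration in the reverse order.

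The Analyses section gives this question one sentence: "The association between working memory and the outcome of therapy is performed by analysis of covariance" and multiple regression. It lists no covariates for that analysis. No size is given anywhere for an order effect.

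**The concern.** Counterbalancing answers a group question: do eye movements slow responses on average? With half the sample in each order, practice or fatigue cancels in the mean difference. The article uses the score for a different question, namely whether people who are taxed more respond differently to treatment. Nothing cancels there, because each person contributes one score from one order. Those with the eye-movement block first carry the order effect with one sign and those with it second carry the other. The result is extra spread in the predictor that has nothing to do with outcome.

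Extra spread of this kind shrinks slopes and correlations and costs power in both the predictor and the moderator analysis. The stated purpose, control of carry-over, is therefore not met by counterbalancing alone for the stated use. A reader of the two sections could reasonably believe that order has been dealt with.

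**Working it through.** **The plan's own figure.** The article gives no sample size for the working-memory analysis. Its only calculation is for the whole trial: "An F-test over three groups with a medium effect-size of treatment compared to waiting list, alpha .05 and power .80 needs 159 participants". Taking medium as f = 0.25 (assumed), a three-group F-test with N = 159 has power 0.805, and 159/(1 − 0.33) = 237.3, or 238 rounded up, against the planned 240. Both figures reproduce. They are used here only to set n: two treated arms of 80 give 160, and 33% attrition leaves 160 × 0.67 ≈ 107.

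**Model.** Write the observed score as D = T + sδ. T is the score free of the order effect, s is +1 or −1 for the two orders in equal shares, and δ is half the difference between the orders' mean scores. Let SD be the within-order SD of the observed score and k = δ/SD. Then:

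- Var(D) = SD²(1 + k²)
- correlation with outcome is multiplied by 1/√(1 + k²)
- regression slope is multiplied by 1/(1 + k²)

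**Size.** The values of k and the true correlation r are assumptions. Power is by Fisher z, two-sided 0.05: Φ(atanh(r)·√(n − 3) − 1.96).

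| Orders differ by (SD) | k | Correlation × | Power, r = 0.20, n = 160 | Power, r = 0.20, n = 107 | Power, r = 0.30, n = 107 |
|---|---|---|---|---|---|
| 0 | 0 | 1 | 0.719 | 0.543 | 0.884 |
| 0.2 | 0.10 | 0.995 | 0.715 | 0.539 | 0.881 |
| 0.5 | 0.25 | 0.970 | 0.692 | 0.518 | 0.864 |
| 1.0 | 0.50 | 0.894 | 0.620 | 0.454 | 0.801 |
| 2.0 | 1.00 | 0.707 | 0.430 | 0.306 | 0.594 |

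**Check by simulation** (4,000 runs, n = 160, true slope 0.25). The unadjusted slope was 0.236, 0.200 and 0.123 at order differences of 0.5, 1.0 and 2.0 SD. The formula gives 0.25/1.0625 = 0.235, 0.25/1.25 = 0.200 and 0.25/2 = 0.125. With order in the model the slope was 0.25 each time. The extra term costs almost nothing: power 0.716 against 0.719 at n = 160 with r = 0.20.

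**Moderator model.** Suppose the outcome depends on arm × T with coefficient d. Since T = D − sδ, this equals d·arm·D − dδ·arm·s. An order main effect alone cannot absorb the arm-by-order term, so the estimated interaction stays at d/(1 + k²). With d = 0.50 that is 0.50/2 = 0.25 at k = 1 and 0.50/1.25 = 0.40 at k = 0.5, with or without order as a covariate. Simulation gave the same values. It returned 0.50 only when order and arm-by-order were both entered, or when the score was centred within order.

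**The case against.** The sentence on counterbalancing is sound for the average contrast it sits beside. Counterbalancing also makes order independent of outcome, so order cannot confound the association. The Analyses section lists no covariates for this question, and a condensed article may leave them to a fuller plan that already contains an order term. All of that stands. What remains is that the article names a control and its purpose, and that this control alone does not achieve the purpose for an individual-level predictor.

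The effect may also be small. k is half the difference between orders, so k = 0.5 already means a full SD apart. If k is instead measured against the SD of error-free taxing, the loss is smaller. At an assumed reliability of 0.5 the multiplier is 1/√(1 + k²/2), which is 0.94 at k = 0.5 and 0.82 at k = 1, rather than 0.89 and 0.71. This stands too, and is why k is defined here on the observed score.

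A reader might infer that a null finding on the working-memory account of EMDR could be blamed on task order. The documents do not support that. They give no order effect, and sample size alone would make a null likely. In one arm, 80 × 0.67 ≈ 53 patients with an assumed r of 0.27 give Φ(0.277 × √50 − 1.96), about 50% power, with no order effect at all.

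**Conclusion.** The point holds as a minor, conditional one. If block order shifts RIR scores, using the score unadjusted attenuates its association with outcome. The loss is about 3% of the correlation or less when the orders differ by up to 0.5 SD, and about 11% at 1 SD. It is nil if there is no order effect. The figures rest on an additive order effect, equal numbers in each order, and assumed values of k and r.

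The bias is toward the null and touches one exploratory, quaternary variable; the CAPS outcome and the treatment comparisons are unaffected. A reader might also conclude that counterbalancing was a mistake, or that order as a simple covariate settles everything. Neither follows. Counterbalancing suits the group contrast and keeps order separable from taxing, and a simple order covariate repairs the predictor models but not the interaction.

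**What to change.** Record the block order each participant received. Then do one of the following:

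- Centre the RIR score (reaction-time slowing and accuracy alike) within order group before it enters any predictor or moderator model.
- Enter order as a covariate in predictor models, and both order and arm-by-order in moderator models.

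State in the RIR description that order is counterbalanced and is also accounted for in every analysis of individual differences.

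The cost is one degree of freedom in a predictor model and two in a two-arm moderator model, with no new data collection beyond keeping the order on file. Neither option removes carry-over that differs from person to person, and the report should say so.

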### Randomization

All patients meeting the inclusion criteria are asked for written informed consent to participate in the intervention study. Consenting participants receive the pre-treatment (T0) measurements. (Note that for patients with auditory hallucinations six days of T0 measurements on auditory verbal hallucinations are added, using ESM; see Instruments). After T0, participants are randomized to PE, EMDR or the waiting list. A group of fifteen random assignments for each participating therapist will be made. These groups are made using the scientific randomization program on the Internet (http://www.randomizer.org) by the independent randomization bureau of the Parnassia Psychiatric Institute. Each block has five assignments for each condition: PE or EMDR or waiting list. Thus, each therapist treats five people with PE and five people with EMDR. After six months, the therapist will offer the five people from the waiting list the therapy of their choice.

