First, the T.TIP Therapist attitude questionnaire (T-TAQ) aims to measure therapist attitude towards the treatments (PE and EMDR). This has two goals: (i) to study therapist treatment attitude as a predictor variable on treatment outcome, and (ii) to study the impact of training and experience on therapist treatment attitude. The T-TAQ is repeatedly administered in the context of training and supervision sessions. The T-TAQ consists of 15 items, divided into three parts a, b (with within session extension) and c (with within session extension). (a) The Impact of Training and Therapeutic Experience Questionnaire – therapist form (ITTEQ-TF) assesses the therapist factor of ‘Training and therapeutic experience’ in PE and EMDR. In this three item therapist self-report list, therapists disclose on a 1 (‘totally disagree’) to 10 (‘totally agree’) VAS their level of (1) training in EMDR/PE, (2) experience in carrying out EMDR/PE and (3) the number of patients treated successfully using EMDR/PE. (b-1)The Credibility Scale- therapist form (CS-TF). Therapists respond to five treatment credibility statements regarding PE and EMDR on a 1 to 10 VAS: (1) This treatment seems logical to me. (2) This treatment seems scientific to me. (3) If I have a PTSD, I would choose this treatment. (4) This treatment would be effective for most people. (5) If a close friend or relative has PTSD, I would recommend this therapy to them. The CS-TF is an adaptation of the original Credibility/Expectancy Questionnaire [118] which demonstrated high internal consistency within each factor (credibility and expectancy) and good test–retest reliability. (b-2) The Credibility Scale- therapist session form (CS-TSF) is an adaptation of the CS-TF. It is an extra 10-item credibility rating that will be applied within actual treatment sessions (1 and 8); the therapist rates not only his or her own opinions on credibility, but in addition makes an estimation of how he or she expects the participant to rate the credibility of the treatment on the same five questions of the CS-TF ('logical' and so on). (c-1)The Burden Scale-therapist form (BS-TF). Seven questions regarding PE and EMDR assess ‘Perceived barriers’ on a 1 to 10 VAS: (1) PTSD will get worse, (2) psychosis will get worse, (3) other comorbid symptoms will get worse, (4) the treatment is a burden to the patient, (5) the treatment is a burden to the therapist, (6) the treatment will facilitate drop out, (7) the treatment will facilitate crisis or admissions to hospital. The BS-TF is inspired by studies that compare the burden and endorsement of CBT and EMDR (for example, studies using the Distress/Endorsement Validation Scale (DEVS)) [119,120]. The BS-TF is not an adaptation of the DEVS, however. It is adapted to suit the research questions of the study regarding (perceived) barriers for treatment in the population of patients with psychosis. There are no psychometric evaluations available. (c-2) The Burden Scale- therapist session form (BS-TSF) is an adaptation of the BS-TF. It is an extra three-item burden rating that will be applied within actual treatment sessions (1 and 8); the content is limited to estimations by the therapist of how he or she expects the participant to rate the burden of the treatment on a 1 to 10 VAS (‘no, not at all’ to ‘yes, very much’): (1) Does the participant fear treatment?, (2) Is he or she hesitant to have this treatment?, and (3; only for PE) Does the participant expect that listening to the recordings at home will be a burden?

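### Therapist attitude, scored on the therapist, is to be tested as a predictor of patient outcome by a regression with no therapist level named, which understates the standard error if therapists differ

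*Protocol article*

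**What the plan says.** In the section on moderators, mediators and predictors, one of two goals of the T-TAQ is "i) to study therapist treatment attitude as a predictor variable on treatment outcome". The questionnaire covers training and experience (ITTEQ-TF), credibility of PE and EMDR (CS-TF) and perceived barriers (BS-TF). It is filled in by the therapist, away from any individual patient: "The T-TAQ is repeatedly administered in the context of training and supervision sessions".

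The Analyses section has one sentence for this class of variable: "The predictors will be assessed with (logistic) regression analysis". The same paragraph names linear mixed models for the primary and secondary outcomes and a multilevel model for the experience-sampling data: "The ESM data will be analyzed by multilevel linear regression modeling using STATA".

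The Randomization section makes patients within therapists part of the design: "A group of fifteen random assignments for each participating therapist will be made", and "Thus, each therapist treats five people with PE and five people with EMDR". The sample size section sets the total: "The needed number of participants is 240. We will use 3 x 80 participants". The article states neither the number of therapists nor a therapist ICC.

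**The concern.** A general attitude score is shared by all patients of one therapist, or by all patients whom that therapist treats with the same method. A regression over patients counts each patient as separate information on that score. If outcomes differ between therapists for any other reason, such as skill, site or case mix, the standard error of the attitude coefficient is too small. Chance alignment between attitude and therapist differences is then declared significant too often.

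The result matters for interpretation. The Background describes clinicians' reluctance to offer trauma treatment, the barrier items mirror those fears, and the Discussion expects predictor findings to inform clinical practice. A spurious link could steer training. A null result from few therapists could be misread as evidence that attitude does not matter.

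**Working it through.** **Inputs from the protocol article.** Total 240, in three arms of 80; 15 assignments per therapist, of which 5 PE and 5 EMDR; attrition 33%; "An F-test over three groups with a medium effect-size of treatment compared to waiting list, alpha .05 and power .80 needs 159 participants".

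**Assumptions, not in the documents.** Therapist ICC of .01, .05 or .10; equal numbers of patients per therapist; one attitude score per therapist, except where noted.

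**1. The plan's own figure.** A one-way F-test with three groups, f = 0.25 (the usual reading of a medium effect) and alpha .05 needs N = 159 (power .805; N = 156 gives .797). Then 159 / (1 − .33) = 237.3, or 238, close to the stated 240. The sample size reproduces. It concerns the treatment comparison and does not cover the predictor question.

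**2. Structure.** 240 / 15 = 16 therapists, and equally 160 treated / 10 = 16, if every block is filled. Treated patients per therapist: m = 10, or 10 × .67 = 6.7 after attrition.

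**3. False-positive rate if patients are taken as independent.** For a score that is constant within therapist, the design effect is DEFF = 1 + (m − 1) × ICC. The actual rate of a nominal two-sided 5% test is 2 × [1 − Φ(1.96 / √DEFF)].

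| ICC | DEFF, m = 10 | Rate | DEFF, m = 6.7 | Rate |
|---|---|---|---|---|
| .01 | 1.09 | 6.1% | 1.057 | 5.7% |
| .05 | 1.45 | 10.4% | 1.285 | 8.4% |
| .10 | 1.90 | 15.5% | 1.57 | 11.8% |

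Simulation with 16 therapists of 10 patients agrees. Linear regression rejects in 6.1%, 10.3% and 15.4% (10,000 runs each). Logistic regression rejects in 9.7% and 13.7% at latent ICC .05 and .10 (2,000 runs each).

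**4. Separate PE and EMDR ratings.** If the two ratings of a therapist correlate .5, the simulated rates at m = 10 are 8.8% (ICC .05) and 12.5% (ICC .10). If they are independent, the rates are 7.6% and 9.8%.

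**5. Does the number of therapists drive the inflation?** No. With 24 therapists of 10 patients each, the simulated rate at ICC .10 is 15.8%, against 15.4% with 16.

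**6. What the number of therapists does limit.** By Fisher's z with 16 units, the correlation detectable with 80% power is tanh((1.96 + 0.84) / √(16 − 3)) = tanh(0.777) ≈ .65.

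**7. The remedy.** Regression on 16 therapist means (14 degrees of freedom), with 10 patients each, rejects in 4.9% to 5.5% for ICC 0 to .15.

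**The case against.** The strongest reply is that the article is condensed. One sentence covers all predictors, it does not say that patients are treated as independent, and no random-effects structure is given for any model, including the primary one. A therapist term could sit in an analysis plan that is not shown. This stands in part: a reader may infer that the authors chose a single-level regression, but the text does not use such a word. What remains is that the article does name a method for predictors, in a paragraph that names mixed or multilevel models for other data. Followed as written, that method does not fit the one group of predictors measured on therapists.

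A second reply is that the scores are not all fixed within a therapist. The T-TAQ is repeated, its session versions are completed in treatment sessions one and eight, and the TPE-TS is scored for each patient. This is correct. Scores that vary among one therapist's patients are inflated less, so the point is confined to the general ITTEQ-TF, CS-TF and BS-TF scores.

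Third, the objective is quaternary and described as exploratory, with no error rate attached. That stands and lowers the severity.

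**Conclusion.** The point holds as a minor one. If patients are analysed as independent, the nominal 5% test of a therapist-level attitude score has a false-positive rate of roughly 6% to 16% for assumed ICCs of .01 to .10 with 10 patients per therapist. After the stated attrition it is about 6% to 12%. It is lower again when PE and EMDR ratings differ within a therapist.

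Three stronger readings are not supported:

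- A reader might take 16% as a ceiling or as a figure from the protocol. It is neither. It depends on the assumed ICC, and at ICC .15 with 10 patients the formula gives 20.1%.
- A reader might blame the inflation on having only 16 therapists. Step 5 shows otherwise: patients per therapist and the ICC cause it, while few therapists limit power. Sixteen is itself derived; unfilled blocks would mean more therapists with fewer patients each.
- A reader might extend the criticism to the treatment comparison. The primary and secondary outcomes have their own models, and nothing here bears on them.

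**What to change.** Add one sentence to the Analyses section, limited to predictors measured on the therapist (ITTEQ-TF, CS-TF, BS-TF). These should be tested in a linear or logistic mixed model with a random therapist intercept and therapist-level degrees of freedom. Alternatively, outcome means per therapist, or per therapist and treatment with therapist clustering kept, can be regressed on the score. The rating occasion used should be named, because the T-TAQ is repeated. The result should be reported as exploratory, with the number of therapists given as the effective sample. If an unseen analysis plan already contains a therapist term, a cross-reference is enough.

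No new data are needed, since the randomization block identifies the therapist. The cost is wider confidence intervals and a plain admission that, with about 16 therapists, only a strong association (a correlation of about .65) is likely to be detected.
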